### Sample size

Ten of the 24 people with dementia included in the pilot test (42%) were classified as having experienced some form of abuse during the past 12 months. This number is similar to previous research concerning abuse of people with dementia [15, 45] and was used for the sample size calculation. The sample size was calculated from tables presented in a study by Bujang and Adnan [4]. In their study, they constructed a formula for estimating sample size for different combinations of estimated prevalence, sensitivity and specificity for screening and diagnostic instruments. For screening instruments, the sensitivity of the instrument is more important than the specificity. According to Bujang, 67 participants are needed to test a screening instrument that has 80% sensitivity at 40% prevalence rate. To assure that the sample size is sufficient, if the sensitivity or prevalence rate is smaller than expected, we aimed at including 80 pairs of participants, i.e. 80 people with dementia and 80 next of kin.

### Statistical analysis plan

#### Aim 1: Testing the validity of REAGERA-S20 and REAGERA-N

Primary outcomes:Criterion validity will be assessed by calculating sensitivity, specificity, positive and negative likelihood ratio as well as positive and negative predictive value of each tool using the final classification made after interviewing both the person with dementia and the next of kin, i.e., the previously described step 7. Only participants for which data is available from both the person with dementia and next of kin will be included in the analyses. For REAGERA-S20, one or more positive answers in part two will be classified as reporting abusive experiences during the past 12 months. One or more positive answers in part three will be classified as abusive experiences earlier in life. For REAGERA-N, one or more positive answers to items concerning perpetration of abuse by next of kin in part two (no 1,3,6–8, 10) or any of the items in part three about witnessing abusive acts will be classified as abuse of the person with dementia during the past 12 months. Affirmative answers to items in part four will be classified as abusive experiences from earlier in life.Test the predictive value of the introductory screening questions in part one of each instrument to identify abusive experiences as identified in part two as well as the final classification of participants as abused or not abused. The introductory screening questions are answered on a three-point ordinal scale (“never,” “sometimes,” “often”). A sum score will be calculated for all items and the best threshold for discriminating between abused and not abused participants will be calculated using a Receiver Operating Curve (ROC) Analysis. We will also examine if one item or a combination of specific items are most likely to predict abusive experiences.

Secondary outcomes:

Sensitivity, specificity, positive and negative likelihood ratio as well as positive and negative predictive value for REAGERA-S20 using only information given in the individual interview with the person with dementia as the gold standard.Sensitivity, specificity, positive and negative likelihood ratio as well as positive and negative predictive value of REAGERA-N for all participants, e.g. also including next of kin to people with GDS score ≥ 6 or people with dementia that were excluded for some other reason. The interview with next of kin will be used as a gold standard and the following classification of abuse according to REAGERA-N will be made: a) one or more positive answers to items 2,4,5 and 9 in part two about abusive behaviours by the person with dementia will be classified as next of kin’s own exposure to abuse during the past 12 months, b) one or more positive answers to items 1,3,6–8, 10 about abusive behaviours towards the person with dementia will be classified as own perpetration of abuse during the past 12 months, c) one or more positive answers to the items in part 3 will be classified as witnessing abusive experiences during the past 12 months and d) one or positive answers in part 4 will be classified as reporting that the person with dementia has been exposed to abuse earlier in life.When there is no established gold standard for a concept, one way to ensure construct validity of a new measurement is to test hypotheses about expected associations with established outcome measurements of related concepts [31]. Care dependence is a well-established risk factor for AOP [5, 15, 25, 40, 49] and we therefore expect to find an association between reporting experiences of abuse and reporting higher scores on ZBI as well as FAQ.

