### Revision of instruments

As a result of the pilot test, a continuing discussion with health and social care professionals and the simultaneous publication of an independent evaluation [19] of the original version of REAGERA-S [39] in social care, a substantial revision of the instruments was performed. In particular, the structure of the instruments was changed in two ways. 1) The life-course perspective originally used for all items was replaced by one part about abusive experiences during the past 12 months and another part about abusive experiences earlier in life. 2) A few introductory screening items to assess risk of abuse were included to limit the number of questions used for those with low risk of abuse.

Also, the first versions of the instruments were only targeted at people with dementia and their relatives, which was mentioned in the introductory text. To simplify for end users, i.e. making it possible for health and social care workers to use the same instrument regardless of cognitive status of the respondent, the introductory text was changed to fit next of kin to all adults with some form of care dependence (REAGERA-N) and all adults (REAGERA-S20) respectively.

The revised versions of the instruments were thereafter evaluated in a renewed Delphi-like procedure. In total, 33 professionals and researchers assessed the instruments’ comprehensiveness and rated the items on relevance and comprehensibility using an online questionnaire. The items were generally given high scores and only minor changes to the instruments were made because of the responses.

As a final step, the two instruments were again tested with cognitive interviews [1], using the same procedure as previously described. This time, six people with dementia and six next of kin were included. Again, minor changes to the wordings were made in accordance with the results of the interviews.

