### Final version of the instruments and intended use

The final versions of REAGERA-S20 and REAGERA-N can be found in the supplement.

REAGERA-S20 contains three different parts. Part 1) Three introductory screening questions to assess risk situations for abuse. Part 2) Twelve questions about exposure to different forms of abuse during the past 12 months. Part 3) Five questions about previous life-course experiences of abuse.

The REAGERA-N consists of four different parts. Part 1) Four introductory screening questions to assess risk situations for abuse. Part 2) Four questions about own exposure to abuse by the person with dementia and six questions about own perpetration of abuse during the past 12 months. Part 3) Seven questions about witnessing abusive experiences towards the person with dementia from third parties, e.g. other relatives or care professionals, during the past 12 months. Part 4) Five questions about experiences of abuse from earlier in life for the person with dementia.

For both instruments, the intended use is that positive responses to the introductory screening questions in part one should lead to using the second part of the questionnaire. Part three in the REAGERA-S20 and part four in the REAGERA-N are intended to be used when a life-course perspective is deemed relevant. The questions in part three in REAGERA-N, about witnessing abusive experiences, may be used when an older person is not able to answer questions themselves, e.g. due to severe cognitive impairment or poor physical functioning.

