An overview of the data collection procedure is given in Fig. 2 and presented in full as follows:At the research visit, participants are placed in different rooms and individually answer the questionnaires REAGERA-S20 and REAGERA-N respectively. The next of kin are also asked to complete the following scales and questionnaires: the UCLA loneliness scale [24], the ZBI [20], the FAQ [35], the NPI-Q [9], the relationship reward questionnaire [46] and the CAMI [13, 34].Semi-structured interviews are then conducted with the person with dementia and their next of kin separately and simultaneously. The two researchers conducting the interviews are blinded to the answers given by the participants in the questionnaires. The interview starts with general background questions and moves on to questions about exposure to abuse. Initially, open-ended questions about negative experiences and difficulties in the relationship are asked. Thereafter, a more structured part of the interview is conducted in which specific questions about physical, psychological, sexual and financial abuse as well as neglect are asked. A digital interview guide is used, in which the researcher records the answers given by the participant to questions about different forms of abuse. If the participant reveals any kind of abusive experiences, an in-depth qualitative interview about the experiences is conducted at any time during the interview. Interviews are recorded and transcribed verbatim which allow for a later review of content as well as qualitative analyses. For the person with dementia, the questions in the Tilburg Frailty Indicator [18, 29] and relationship reward questionnaire [46] are also included in the interview.At the end of the individual interviews, the researchers check the answers given by the participant in REAGERA-S20 or REAGERA-N and compare them to the responses recorded in the digital interview guide during the interview. This allows for clarification of inconsistent responses and a preliminary classification of the person with dementia as abused or not abused based on the information provided in each individual interview.After the individual interviews have been completed, the two researchers compare the results from each interview. If needed, and with permission obtained individually from the participants, a joint concluding interview is conducted. This interview again allows for clarifying possible inconsistencies.After the interviews are completed, the two researchers together make a new classification of abuse status, considering information from both interviews. It is also noted if abuse earlier in life happened before the age of 18, between 18 and 60 or after the age of 60. In addition, the type of relationship with the perpetrator is noted. This information is collected to be able to understand false negatives, i.e. what types of abusive experiences are not captured by the REAGERA-S20 and REAGERA-N.One follow-up phone call is made after the interview to inquire about negative effects of participating in the study or if participation has given rise to any thoughts or questions. If there are indications of emotionally stressful or traumatic reactions of participating in the interview, relevant referrals to societal resources can be made at this stage.All interviews are recorded and transcribed verbatim. Thereafter, a review of the classification of participants as abused or not abused made during the interviews is conducted, using the transcript as a reference. The review is made by at least two researchers to make sure that similar classifications are made for all participants concerning kinds of experiences that constituting abuse. The final classification will be used as the gold standard against which the validity of the screening instruments is measured. If there is doubt whether an experience should be classified as abusive or not, discussions will be held within the research group and the Toronto Declaration [44] and the CDC definition and core elements of elder abuse [23] will additionally be used for the assessment. The following classification is used:For the person with dementiaReporting or not reporting abusive experiences during the past 12 months.Reporting or not reporting abusive experience earlier in life, i.e. more than 12 months ago.For the next of kinReporting or not reporting own exposure to abuse by the person with dementia during the past 12 months.Reporting or not reporting own perpetration of abuse towards the person with dementia during the past 12 months.Reporting or not reporting that the person with dementia has been exposed to abuse by another person during the past 12 months.Reporting or not reporting that the person with dementia has been exposed to abuse earlier in life, i.e. more than 12 months ago.

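### For 12-month abuse, the primary accuracy figures score part two without the part-one gate, so they do not give the accuracy of the two-stage sequence the instruments are meant to follow

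*Protocol article*

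**What the plan says.** The section on the final version and intended use describes a two-stage procedure. It covers REAGERA-S20 and REAGERA-N alike: "the intended use is that positive responses to the introductory screening questions in part one should lead to using the second part of the questionnaire". The section on revision of the instruments gives the reason: the introductory items were added "to limit the number of questions used for those with low risk of abuse".

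The statistical analysis plan, Aim 1, promises sensitivity, specificity, likelihood ratios and predictive values for each instrument against the final classification. Its 12-month scoring rules do not mention part one. For REAGERA-S20: "For REAGERA-S20, one or more positive answers in part two will be classified as reporting abusive experiences during the past 12 months". For REAGERA-N, a pair is positive on a part-two perpetration item, or "any of the items in part three about witnessing abusive acts will be classified as abuse of the person with dementia". The intended-use section says that REAGERA-N part three "may be used when an older person is not able to answer questions themselves".

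Part one has its own primary outcome: "Test the predictive value of the introductory screening questions in part one of each instrument to identify abusive experiences as identified in part two", and also against the final classification. The cut-off on its sum score is to be found by ROC analysis.

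On administration, the procedure section says that "participants are placed in different rooms and individually answer the questionnaires REAGERA-S20 and REAGERA-N respectively". It describes no skipping of part two.

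**The concern.** A user who follows the intended-use section asks part two after a positive part one. Someone stopped at part one then counts as negative, whatever they would have answered in part two. The primary rule counts that same person as positive. The sensitivity reported for the instrument can therefore be more favourable than the sensitivity of the recommended sequence.

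The article itself makes this the property that matters. The sample size section ranks sensitivity above specificity for screening. The pilot section reports that most misclassified cases were negative on the instrument and positive at interview, and concludes that sensitivity had to improve. The gate was added in the revision that followed. Compared with asking part two of everyone, a gate can only add false negatives, and the first primary outcome as scored cannot show them.

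**Working it through.** **Inputs from the article (Sample size).** Planning sensitivity 80%, planning prevalence 40%, target 80 pairs. The pilot prevalence reproduces: 10/24 = 41.7%, reported as 42%. The figure of 67 participants cannot be reproduced, because the article gives no null sensitivity, significance level, power or precision for it. Nothing below uses it.

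**Assumptions, not in the article.** The share g of part-two true positives who also pass the gate; part-two specificity of 80%; gate specificity of 50% to 80%.

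**Step 1, direction.** Let A be abused by the final classification, T2 a positive part two and G a positive part one. For REAGERA-S20:

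Se(gated) = P(G and T2 | A) = P(T2 | A) × P(G | T2, A) = Se(part two) × g

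Since g is at most 1, Se(gated) cannot exceed Se(part two). They are equal only if the gate stops no part-two true positive.

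**Step 2, size from the planning sensitivity.** Se(gated) = 0.80 × g:

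| g | 1.00 | 0.95 | 0.90 | 0.85 | 0.80 | 0.70 |
|---|---|---|---|---|---|---|
| Gated sensitivity | 80% | 76% | 72% | 68% | 64% | 56% |

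**Step 3, in people.** 80 × 0.40 = 32 abused. 32 × 0.80 = 25.6, so about 26 are detected by part two (26/32 = 81.3%). Each one stopped at the gate costs 1/32 = 3.1 points: one gives 25/32 = 78.1%, three give 23/32 = 71.9%, five give 21/32 = 65.6%. If people pass independently, the chance that the gate stops none of the 26 is 0.95^26 = 26% at g = 0.95 and 0.90^26 = 6% at g = 0.90.

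**Step 4, the other measures.** With part one and part two independent among the non-abused, Sp(gated) = 1 − (1 − 0.80) × (1 − gate specificity). That is 1 − 0.20 × 0.50 = 90% at gate specificity 50%, and 1 − 0.20 × 0.20 = 96% at 80%. At 40% prevalence, taking g = 0.90 and gated specificity 96%:

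- PPV goes from 0.32/(0.32 + 0.12) = 72.7% to 0.288/(0.288 + 0.024) = 92.3%.
- NPV goes from 0.48/(0.48 + 0.08) = 85.7% to 0.576/(0.576 + 0.112) = 83.7%.
- The negative likelihood ratio goes from 0.20/0.80 = 0.25 to 0.28/0.96 = 0.29.

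The gate therefore does not make every measure worse.

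**Step 5, whether the planned part-one analyses already give the answer.** They yield the gate's sensitivity against the final classification, and a part-one by part-two comparison that is not split by abuse status. Suppose the gate's sensitivity is 90% and that of part two is 80%. The joint sensitivity then lies between 0.90 + 0.80 − 1 = 70% and min(0.90, 0.80) = 80%. The two margins leave a 10-point range.

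**Step 6, REAGERA-N.** Only the part-two component is gated. The rule with the gate is (G and a perpetration item) or part three. It differs from the planned rule only for people who are gate-negative, positive on a perpetration item and negative throughout part three. The direction is the same, but anyone positive on part three is unaffected, so the Step 2 figures apply directly only to REAGERA-S20.

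**The case against.** The strongest reply is that the gate is already a primary outcome. Abused people whom part one misses will be counted, and so will part-two positives whom it misses. That is correct. A reader might infer that losses at the gate would be invisible, and the article does not support that. What is absent is the combined result.

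Second, no gate exists yet. The cut-off is to be derived, single items and combinations will be explored, and testing part two in everyone while deriving the gate is a sensible order of development. This stands as a reason to add a named analysis rather than replace the primary rule. It also means that a gated figure using a cut-off chosen on the same pairs would be optimistic.

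Third, an article may leave extra tables to a fuller plan. That does not dispose of the point, because the scoring rule is stated here and the resulting figures are presented as the accuracy of the instrument whose intended use is described differently.

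Fourth, a reader might infer that counting REAGERA-N part three in these pairs contradicts the intended use, since the person with dementia does answer. The wording is permissive: it names a situation in which part three may be used and excludes no other. The secondary outcomes also report perpetration and witnessing separately, although against the next-of-kin interview. No contradiction is established.

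Finally, that everyone answers part two is an inference from the procedure section and from the part-one versus part-two comparison, which needs answers from gate-negative people. It is a reasonable inference, but the article does not say so outright.

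**Conclusion.** The point holds for the 12-month classification and should be fixed. The reported sensitivity cannot be lower, and the reported specificity cannot be higher, than those of the gated sequence. A reader might infer that sensitivity will certainly be overstated. It is overstated only if at least one abused person who is positive solely through part two is gate-negative. That is likely with about 26 part-two true positives unless the gate is close to perfect, but it is not certain.

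The size cannot be known in advance. The 72% and 64% illustrations rest on the planning sensitivity of 80% and on assumed pass rates of 90% and 80%; the specificity and predictive-value illustrations also rest on assumed specificities and conditional independence. The earlier-life classifications are not gated by part one and are not affected.

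**What to change.** - Label the current 12-month figures as part two administered to all; for REAGERA-N, as perpetration items or part three administered to all.
- Add a named analysis, against the final classification, of the gated rule: part one at or above the cut-off and at least one positive part-two item. For REAGERA-N, apply the gate to the perpetration items. Report the same accuracy measures.
- Use a cut-off stated in advance, for example any part-one answer other than never. If the cut-off is chosen by ROC on the same pairs, correct for optimism, for example by bootstrap.
- State that all participants answer part two whatever they answered in part one.
- As a minor addition, show REAGERA-N in the pairs with and without part three against the final classification.

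The cost is a few sentences and one extra table from answers already collected. The downside for the authors is that the gated sensitivity may look less favourable than the ungated one.

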#### Aim 2: Validity testing of the Swedish version of the REAMI

The risk of abuse is assessed on a four-point scale on the REAMI (“no risk,” “low risk,” “moderate risk” and “high risk”). The final classification of participants as abused or not abused will be used as a gold standard and a ROC analysis will be used to investigate the threshold for which the REAMI best can discriminate between abused and non-abused participants. Sensitivity, specificity, positive and negative likelihood ratio as well as positive and negative predictive value will then be calculated for that value. As the REAMI was also included in the pilot study and has not been revised since, this analysis will also include the twenty-four pairs of participants included in the pilot study.

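### The part-one and REAMI cut-offs are chosen by ROC in the study data and their accuracy is judged in the same participants, so accuracy at the chosen cut-offs will be optimistic

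*Protocol article*

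**What the plan says.** The statistical analysis plan section of the protocol article makes two kinds of accuracy assessment.

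**Rules fixed in advance.** For parts two and three of REAGERA-S20 and parts two to four of REAGERA-N, any single positive answer to the listed items counts as a positive result. Nothing is chosen from the data.

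**Rules chosen from the data.**
- Part one of each REAGERA tool (Aim 1, primary outcomes). The predictive value of the introductory questions is tested against part two and against the final classification. Items are summed and "the best threshold for discriminating between abused and not abused participants will be calculated using a Receiver Operating Curve (ROC) Analysis". The next sentence reads: "We will also examine if one item or a combination of specific items are most likely to predict abusive experiences".
- REAMI (Aim 2). The four risk categories enter a ROC analysis to find the best-discriminating threshold. "Sensitivity, specificity, positive and negative likelihood ratio as well as positive and negative predictive value will then be calculated for that value". The 24 pilot pairs are added to this analysis; they are not set aside to test the threshold.

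The section on the final instruments gives the number of part-one items: "Three introductory screening questions to assess risk situations for abuse" for REAGERA-S20 and "Four introductory screening questions to assess risk situations for abuse" for REAGERA-N. The sample size section states that "we aimed at including 80 pairs of participants, i.e. 80 people with dementia and 80 next of kin".

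**The concern.** For the REAMI, selection and evaluation in the same participants is explicit. For part one it follows from choosing the threshold and testing predictive value in the same pairs. In both cases the chosen rule partly fits chance features of the sample, so the quantity that the selection maximised is overstated on average.

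This matters most for part one. In the intended use, positive answers there lead to part two. A person below the chosen cut-off would not be asked about abuse, so overstated sensitivity means more missed abuse than the report suggests. The sample size section itself ranks sensitivity above specificity for screening. Nor can pilot data serve as a test set for part one, because the introductory questions were added in the revision after the pilot.

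**Working it through.** **The plan's own figure.** The article gives no expected accuracy for part one or the REAMI. Its one calculated figure is that "67 participants are needed to test a screening instrument that has 80% sensitivity at 40% prevalence rate". The null value, significance level, power and precision behind 67 are not given, so it cannot be tied to one calculation. For example, a 95% half-width of 0.15 gives 1.96² × 0.8 × 0.2 / 0.15² = 27.3 abused, and 27.3 / 0.40 = 68.3 participants. The point here does not depend on 67.

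**Inputs from the article.**
- Part one: 80 pairs. Abused: 80 × 0.40 = 32, or 80 × 0.42 = 34 using the pilot's 10 of 24.
- REAMI: 80 + 24 = 104 pairs, assuming the target is met and every form is returned. Abused: 104 × 0.42 = 44.
- Part-one items have three levels. Coded 0 to 2 (assumed), the sums run 0 to 6 (S20) and 0 to 8 (N), giving 6 and 8 possible cut-offs. Four REAMI categories give 3.
- Non-empty item subsets: 2³ − 1 = 7 (S20) and 2⁴ − 1 = 15 (N).

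**Assumptions not in the article.** The best rule is the one that maximises J = sensitivity + specificity − 1. Prevalence is 42%. Items arise from normal variables with correlation 0.3, and the abused are shifted upward by 0 to 1.5 standard deviations.

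**Method.** Draw a study of the planned size, choose the rule with the highest J, and record its apparent J. Score the same rule in a very large sample from the same population to get its true J. Optimism = mean apparent J − mean true J (1,500 studies per part-one scenario, 3,000 per REAMI scenario).

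Optimism in percentage points of sensitivity + specificity:

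| Rule | Shift 0 | 0.5 | 1.0 | 1.5 |
|---|---|---|---|---|
| S20 part one, cut-off only | 7.6 | 5.4 | 4.7 | 3.8 |
| N part one, cut-off only | 8.1 | 6.1 | 5.1 | 4.1 |
| REAMI, 104 pairs | 5.6 | 5.1 | 3.8 | 3.1 |
| S20 part one, all subsets and cut-offs | 11.8 | 10.8 | 9.7 | 6.7 |
| N part one, all subsets and cut-offs | 14.2 | 13.5 | 11.7 | 9.2 |

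At shift 1.0, as apparent sensitivity/specificity against the values in new participants:
- N part one, cut-off only: 75.6/78.2 against 72.8/75.8.
- REAMI: 69.4/70.2 against 67.1/68.7.
- N part one with the full subset search: 78.0/79.5 against 70.9/74.8.

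**Other assumptions.** Simulations with 40% abused gave 4.4 to 6.1 points (part-one cut-off), 9.2 to 14.1 (full subset search) and 2.3 to 3.2 (REAMI). A further run gave about 4 to 8, 10 to 15 and 4 to 5. Together the ranges are 4 to 8, 7 to 15 and 2 to 6.

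**Against sampling error.** For the REAMI at shift 1.0, the 95% half-width for sensitivity is 1.96 × √(0.694 × 0.306 / 44) = 0.136, about 14 points, against a bias of 69.4 − 67.1 = 2.3. For N part one with the cut-off only, it is 1.96 × √(0.756 × 0.244 / 34) = 0.144, again about 14 points, against 75.6 − 72.8 = 2.8.

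**The case against.** The strongest reply is that this is a journal article, and internal validation is a detail commonly left to a fuller plan. That stands as far as it goes: the article's silence does not show that no correction will be made. But the point does not rest on silence. The article commits to a data-chosen threshold and, for the REAMI, to accuracy calculated at it. Followed as written, that procedure gives optimistic figures. If a correction is planned elsewhere, one sentence settles the matter.

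Second, the sentence on items specifies no exhaustive search, no joint choice of subset and cut-off, and no accuracy figure for a winning subset. It could describe item-level associations only. This stands, so the 7 to 15 points are conditional.

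Third, maximising sensitivity plus specificity is an assumption, and the protocol's preference for sensitivity suggests another criterion might be used. This also stands. The size of the bias depends on the criterion, but whatever quantity is maximised in the sample is still overstated there.

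Fourth, where the procedure is most explicit, for the REAMI, the bias is small beside sampling error. That is right, and a cut-off-only choice for part one is also well inside its sampling error. Sampling error, however, goes either way; this bias pushes the maximised quantity one way and is cheap to remove.

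A reader might also infer that the cut-offs will be published as validated, or that their confidence intervals will ignore the selection. The article says neither; its analysis section mentions no confidence intervals.

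**Conclusion.** The point holds for the data-chosen rules only. Accuracy at the ROC-selected cut-offs of part one and the REAMI will be optimistic if calculated as described. If the rule maximises sensitivity plus specificity, that sum is overstated by about 4 to 8 points for the part-one cut-off and about 2 to 6 for the REAMI. The direction was the same in every scenario; the size rests on the assumed criterion, item correlation and true discrimination. The range of 7 to 15 points applies only if the item examination becomes a full search over subsets and cut-offs.

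It would be wrong to conclude that the main criterion-validity results are biased by this. The rules for parts two to four are fixed in advance, and their estimates involve no selection. The change is worth making, but it does not undermine the study's central estimates.

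**What to change.** 1. State the criterion by which a cut-off is judged best. Repeat the whole selection, meaning the cut-off and any choice of items, within bootstrap resamples. Report optimism-corrected sensitivity, specificity and AUC beside the apparent values.
2. Label data-chosen cut-offs and item sets as derived, pending external validation.
3. For the REAMI, report accuracy at all three category boundaries and not only the selected one. The ROC analysis already produces these three points, and reporting them all involves no selection.

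No new participants or data are needed. The cost is a short addition to the plan, a little more analysis work, and slightly less favourable figures.
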